## Methods/Design

We will conduct a randomised control trial of low glycaemic index diet versus no intervention in prevention of recurrence of macrosomia.

The primary outcome measure will be the mean birth weight centiles.

The secondary outcome measure will be the difference between the two groups in maternal weight gain in pregnancy.

The study will be carried out in the National Maternity Hospital, Dublin.

Secundigravid women whose first baby was macrosomic, defined as a birth weight greater than 4000 g will be recruited at first booking visit.

Subjects will be excluded if they have diabetes, other medical disorders and those with poor previous pregnancy outcome.

Patients will be randomised into two groups: a control arm which will receive no dietary intervention and a diet arm which will be commenced on a low glycaemic index diet from 14 weeks gestation to delivery under dietetic supervision.

Randomisation will be achieved using computer generated allocations in a ratio of 1:1 contained in sealed opaque envelopes.

Women choosing to enter the study will give written informed consent. Data will be collected on those women approached for study participation and who declined to ensure those participating are representative of this entire group.

Each patient in the diet arm will receive an individualised diet which will be energy matched as appropriate to a patients average caloric intake with the aim of reducing glycaemic load and glycaemic excursions. This diet is eucaloric and is not designed to promote weight loss. In the diet arm each patient will have one dietetic session, in groups of 4-6 at 12-16 weeks' gestation, with the aim of commencing the diet at 16 week's gestation. At booking visit all patients will have their height and weight recorded and their BMI will be calculated (Maternal weight Kg/Height in metres^2^). Additional demographic data including smoking history, SEG and paternal weight and height will be recorded.

In addition to routine care the following additional tests will be performed.

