Power analysis was performed by [name]. The primary outcome measure is the difference in the birth weight post intervention versus control women, adjusted for birth weight of the first child, i.e. the difference between intervention and control groups in the change in gender and gestational age adjusted birth weight achieved. The sample size required depends on a significance level set at conventional level of 5% and power set at conventional level of 90%. To detect a 0.25 SD difference in birth weight- this is equivalent to a 102 g difference in the birth weights achieved in control and intervention groups one would need 360 women in each group. A sample size of 360 women in each group will have 90% power to detect a difference of at least 100 g in birth weight between control and intervention groups. Thus 720 women will be randomised to 'no intervention' or to 'low glycaemic index diet. Based on 2004 figures at NMH 2700 women annually are secundigravid, with an estimated 20% with a previous baby > 4 kg gives 540 annually available for participation. An estimated 20% (n = 108) will either be ineligible for the study due to inadequate English (14%), history of medical disorder or poor obstetric history (2%), multiple pregnancy (2%), gestational diabetes (2%) leaving 432 women suitable for recruitment. Assuming a 70% participation rate we estimate that up to 300 women annually will be recruited.

This study had received approval from the ethics committee of the National Maternity Hospital (June 2006).

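### The primary outcome equates adjusting for the first baby's birth weight with a difference in change from it; these are different estimators, and the change version is never the more precise

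*Protocol article*

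**What the plan says.** All statements come from Methods/Design in the protocol article.

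- The power paragraph opens with: "The primary outcome measure is the difference in the birth weight post intervention versus control women, adjusted for birth weight of the first child". The same sentence continues: "i.e. the difference between intervention and control groups in the change in gender and gestational age adjusted birth weight achieved". The two halves are offered as one quantity.
- The sample size follows directly: "To detect a 0.25 SD difference in birth weight- this is equivalent to a 102 g difference in the birth weights achieved", and then "A sample size of 360 women in each group will have 90% power to detect a difference of at least 100 g in birth weight". No correlation between siblings' weights, no first-baby SD and no SD of a change appears.
- Entry is restricted to women whose first baby weighed more than 4000 g. The power paragraph puts these at an estimated 20% of women in a second pregnancy. The Background puts recurrence of macrosomia at one third.

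**The concern.** An outcome that is "adjusted for birth weight of the first child" is normally read as a regression in which the data determine how much of the first baby's weight carries over to the second. A difference in change subtracts the whole of the first weight. The two agree only if the true slope is 1. An analyst who follows the second half of the sentence literally would use change scores.

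At stake is precision in the primary comparison. If the slope is well below 1, subtraction adds noise, and if it is below 0.5, a change score does worse than ignoring the first baby. The stated power was worked out for neither the adjusted nor the change analysis. Leaving two definitions in place also leaves a choice of primary estimator open until data are seen.

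**Working it through.** **1. Reproduce the stated sample size.** Inputs: 5% (two-sided assumed, as sidedness is not stated), 90% power, 1:1 allocation, 0.25 SD = 102 g. The implied SD is 102/0.25 = 408 g.

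n per arm = 2(1.960 + 1.282)² SD²/δ²

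- δ = 102 g: 337 per arm; power with 360 is 91.8%.
- δ = 100 g: 350 per arm; power with 360 is 90.8%.

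The protocol's 360 at 90% for 100 g is therefore a plain two-sample comparison of second-baby weights. One-sided figures (275 and 286) do not fit.

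**2. Compare the estimators.** Let b be the slope of second on first weight, V1 the variance of first-baby weight among trial women, and R the residual variance of second-baby weight given the first.

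- Adjusted (analysis of covariance): R
- Unadjusted: R + b²V1
- Change: R + (1 − b)²V1

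Change exceeds adjusted by (1 − b)²V1, which is zero only at b = 1. Change exceeds unadjusted by (1 − 2b)V1, which is positive whenever b < 0.5.

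**3. A plausible slope.** The protocol gives no sibling correlation. Assume bivariate normal weights in unselected women, with 20% of first babies above 4 kg (cut-off 0.842 SD), one-third recurrence, and 20% of second babies also above 4 kg. The last figure is an assumption; the protocol's 20% refers to the previous baby. Solving P(both above) = 0.20/3 gives a correlation of 0.305, which with equal SDs is also b.

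**4. Base case, in units of the unselected variance.** Restricting the first weight to its top 20% leaves V1 = 0.2186.

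- R = 1 − 0.305² = 0.907
- Unadjusted = 0.907 + 0.305² × 0.2186 = 0.927
- Change = 0.907 + 0.695² × 0.2186 = 1.013

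Change/adjusted = 1.013/0.907 = 1.12. Change/unadjusted = 1.013/0.927 = 1.09.

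**5. Convert to grams.** Take 408 g as the in-trial SD of second-baby weight (an assumption). The change SD is 408 × √1.092 = 426 g, and the adjusted SD is 408 × √(0.907/0.927) = 403 g. Power = Φ(δ/(SD√(2/360)) − 1.96). Each cell from the third column on gives unadjusted / adjusted / change.

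| Second babies > 4 kg (assumed) | Slope | SD (g) | n per arm, 90% at 100 g | Power %, 360 per arm, 100 g | Power %, 360 per arm, 102 g |
|---|---|---|---|---|---|
| 15% | 0.46 | 408 / 396 / 412 | 350 / 331 / 357 | 90.8 / 92.3 / 90.2 | 91.8 / 93.2 / 91.3 |
| 20% | 0.31 | 408 / 403 / 426 | 350 / 343 / 382 | 90.8 / 91.4 / 88.2 | 91.8 / 92.4 / 89.4 |
| 25% | 0.18 | 408 / 407 / 436 | 350 / 348 / 401 | 90.8 / 91.0 / 86.7 | 91.8 / 92.0 / 88.0 |

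The variance ratio of change to adjusted is 1.08, 1.12 and 1.15 in the three rows.

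**The case against.** **The loss is small and the comparison stays valid.** This stands. Both analyses estimate the same between-arm difference under randomisation. At 102 g, change-score power in the base case is 89.4%, which is 0.6 points under the target.

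**The shortfall is not certain.** This also stands. A reader might infer that the change analysis must miss 90%, but in the 15% row it reaches 90.2% at 100 g. The meaning of 408 g is also not stated. If it is an SD before sex and gestation adjustment, that adjustment would lower the variance; a cut of about 6% in change-score variance (426 to about 413 g) restores 90% at 100 g. The error could also run the other way. Selection is on raw weight, so adjusted first-baby weights may be less tightly truncated. If their SD were 0.7 of the second-baby SD with an in-trial correlation of 0.2, the ratio of change to adjusted would be (1 + 0.49 − 0.28)/(1 − 0.04) = 1.26.

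**Selection is not the cause.** A reader might infer that choosing women with a first baby over 4000 g creates the low slope or the penalty. It does neither. In a linear model, truncating the first weight leaves the slope unchanged and reduces V1. In unselected women with correlation 0.305 the penalty against adjustment would be 2/(1 + 0.305) = 1.53, that is 53% rather than 12%.

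**No within-arm analysis is planned.** A reader might worry that falls from the first baby to the second would be presented as benefit. The protocol specifies a contrast between arms, and regression to the mean common to both arms cancels from it.

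**Model choice may belong in an analysis plan.** Missing model detail would be no finding. This point does not rest on missing detail: the sentence asserts an equivalence that is false, and a later plan specifying covariance adjustment would contradict it.

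**Conclusion.** The point holds as a misstatement of the primary analysis with a modest cost in precision. That change and adjustment differ, and that change is never more precise, follows from algebra and needs no assumed figures. The size does need them. Under the normal model above, change requires about 12% more women than analysis of covariance (8% to 15% across the assumed recurrence scenarios). If 408 g is the in-trial SD of second-baby weight, power with 360 per arm at 100 g is about 88% for change (86.7% to 90.2%) against 91% for analysis of covariance; at 102 g it is about 89% against 92%. The stated 90% belongs to an unadjusted comparison, and the change analysis may fall slightly short of it. The documents do not support a claim of bias or of certain loss of 90% power.

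**What to change.** Remove the clause that restates the outcome as a change. Define the primary analysis as a regression of second-baby sex- and gestation-adjusted birth weight on trial arm, with first-baby adjusted birth weight as a covariate whose slope is estimated. The sex and gestation adjustment now appears only in the clause to be removed, so it must be carried into the new sentence. Add a few words saying which SD the 408 g represents: raw or adjusted weight, and in which population.

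The cost is a sentence or two. The target of 360 per arm can stay, and first-baby weight is already needed to establish eligibility. Estimating one slope from 720 women costs essentially nothing. This change does not settle whether birth weight or the birth weight centile named earlier in Methods/Design is the primary outcome; that needs its own correction.

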## Discussion

The purpose of this randomised trial is to assess the impact of a maternal eucaloric low glycaemic index diet on birth weight. We will also assess its impact on maternal weight gain in pregnancy. In addition this study will examine the effect of this diet on maternal metabolism, fetal insulin, fetal growth factors and placental development. The results will increase our understanding of the inter-relation between maternal nutrition and pregnancy outcome. If the findings show a beneficial effect of this eucaloric low glycaemic index diet on birth weight and on maternal weight gain, then it may applicable generally to women with increased body mass index, or those at risk of macrosomia. Prevention of macrosomia at birth will help reduce the incidence of childhood and subsequent adult obesity [11]. The outcome of this study will delineate the relationship between maternal nutrition, fetal programming and infant birth weight, and could have a significant impact on the application of public health nutrition policies on maternal and fetal nutrition.
